##### Participants: control intervention

Participants randomized to the control group will receive enhanced usual care. Usual care involves attendance at antenatal and postnatal clinics on a voluntary basis, where the focus is on fetal and infant physical development and immunization. Enhanced usual care will comprise, in addition to usual care, regular monthly telephone calls over 3 months, delivered by two CHWs trained in conducting structured phone calls but not trained in counseling techniques. The telephone calls by the CHWs will engage participants in a brief conversation about i) how the woman is feeling (general health question); ii) whether there are any major changes in the woman’s life and, if so, what these are (including starting any medication); iii) whether she has someone to assist her if she needs help; iv) whether she or her baby have been visited by any community workers from other organizations and description of these visits; and v) whether there is suicidal ideation. If there are signs of major problems (e.g., abuse or other social difficulties), participants will be provided with contact details of relevant health services and NGOs. If there are signs of suicidal ideation, they will be referred to the psychiatric nurses at the clinic. Similarly to the intervention arm, unless their health or behavior makes it impossible for them to continue to receive the telephone calls or participate in follow-up assessments, suicidal participants will be retained in the study.

In determining the optimal number and frequency of phone calls to the women in the control arm, a balance needs to be retained between the need to monitor any adverse changes in the women’s mood, and not being too intrusive or providing too intensive an intervention that would not represent usual care. Following formative research and discussion with the research team, it was decided that monthly telephone calls given over 3 months (in keeping with the timing of the counseling intervention) are sufficiently frequent to monitor any major changes in mood, offer referrals, and provide information about services and thereby constitute enhanced usual care.

##### Fidelity of the control arm

Fidelity will be assessed by the mental health supervisor who will monitor the calls randomly for 1 hour per CHW per week. In addition, the CHW who conducts the calls will be required to complete a checklist, setting out the information covered during the call, any need for referrals, and adverse events.

### Number and duration of visits

Participants in both arms will be screened at baseline and receive follow-up assessments at 1 month antenatally and 3 and 12 months postnatally. Participants in the intervention arm will be asked to attend six counselling sessions, and a sub-sample (n = 36) will be randomly selected to participate in a semi-structured qualitative interview after their 3 month postnatal assessment. The assessments, counselling sessions, and semi-structured interview will each take approximately one hour. A sub-sample (n = 10) of the control arm participants will be randomly selected to participate in a semi-structured qualitative interview after their 3 month postnatal assessment. All participants will be involved in the study for approximately 15 to 18 months (including follow-up assessments).

### Outcomes

#### Outcome measures

The primary outcome measure is depression, assessed using the HDRS 17-item version [50]. Secondary outcome measures will be assessed using the following instruments:

Edinburgh Postnatal Depression Scale (EPDS) [51].Mini International Neuropsychiatric Interview 6.0.0 [52]: Major Depressive Episode and Suicidality modules.A Health Care Utilization Questionnaire, adapted from the Client Socio-Demographic and Service Receipt Inventory – European Version [53], and the Client Service Receipt Inventory [54].World Health Organization Disability Assessment Schedule 2.0 [55, 56].Cape Town Functional Assessment Instrument for Maternal Depression; this instrument has been developed during the formative preparation of the trial, and uses the method for developing a local culturally valid functional assessment instrument developed by Bolton et al. [57].Household Food Insecurity Assessment scale [58].Multidimensional Scale of Perceived Social Support [59, 60].Alcohol Use Disorders Identification Test [61].Brief drug, abuse, and HIV questions: this involves a few questions regarding any drug use, or experience of physical or sexual violence; in addition, participants will be asked to disclose their HIV status.Obstetric and child outcome measures at 3 and 12 month postnatal follow-up assessments. These will include height and weight of the infant, head circumference, adherence to child immunization (marked on the baby’s Road to Health Chart), and prevalence of diarrheal disease and respiratory tract infections.

The above outcome measures will be administered at baseline, at 1 month antenatally, and at 3 months and 12 months postnatally. To our knowledge, participants will not be participating in any other research study, and we will include questions about the receipt of other interventions in all baseline and follow-up interviews.

All assessments will be conducted by trained field workers using handheld electronic devices. This will allow data to be uploaded to a central database in real time, minimize the likelihood of errors at data collection or capturing stages, and will facilitate the continuous checking of data quality by the research officer.

All instruments have been translated into isiXhosa. Some instruments have been used in a number of studies with isiXhosa-speaking participants. The other instruments have been forward and back-translated, and their performance carefully reviewed during the pilot phase.

### Sample size and power calculation

The sample size of 420 women (210 in each arm) is based on the following assumptions: two-sided testing at alpha = 0.05, beta = 0.1 (i.e., 90% power), and a 30 to 50% reduction in depressive symptoms at 3 months postnatally as measured by the HDRS-17 in the control arm based on enhanced usual care. Absolute effect sizes of interest range from 20 to 40%. Based on previous cohort studies and trials in mental health care in this community, we feel that 10% attrition over the study period is realistic. In addition, we conservatively estimate contamination between the trial arms of the order of 5% (that is, 5% of women in the control arm will experience the treatment effect of the intervention through exposure to women in the intervention arm). Based on these assumptions, we estimate that 420 women in the trial will be required to detect an intervention effect of 20% or greater between the two arms.

The sample of 420 women makes provision for subjects that might move away or refuse to take part in the study at a later stage. If subjects in the study drop out or are unable to continue participating in the trial they will not be replaced. Drop out from care is defined as three consecutive missed appointments, for either the counselling sessions or telephone calls. We will endeavor to continue to collect data from people who move out of the area provided they give informed consent to continued participation, and can be contacted. After a participant has missed five consecutive follow-up assessment appointments for a specific assessment point, they will be deemed to have dropped out of the study.

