### Statistical methods

A data management and statistical analysis plan has been developed during the preparations leading up to the trial. This details the procedures for data quality assurance and quality control (including standard operating procedures), data entry, management and cleaning, and data analysis (including *a priori* comparisons, interim analyses, and Data Safety and Monitoring Board (DSMB) instructions).

Data will be entered at the time of interview via handheld devices (cell phones) and automatically stored in a secure firewall-protected database. Data analysis will take place using the latest version of STATA (College Station, Texas, USA). All analyses will be blinded until the analysis is finalized and approved by all investigators. Data cleaning based on frequency distributions and logic checks will follow standard procedures with reference to source documents as required. Exploratory analyses will include frequency distributions and measures of central tendency and dispersion, as appropriate, with 95% confidence intervals. Throughout these analyses, stratifications will be by participant age, and depression severity at enrollment. Throughout, bivariate comparisons will employ χ^2^, Fisher’s exact, student’s T- or rank-sum tests, as appropriate; all statistical tests will be two-sided at α = 0.05. The primary analysis will be by intention-to-treat, and secondary analyses will be on a per protocol population, defined as women who complete all sessions in either arm of the trial. The primary outcome measure will be analyzed using linear regression adjusting for baseline symptom severity measured using the HDRS-17. The validity of regression assumptions will be checked using residual plots. Logistic regression will be used to model some secondary outcomes, which are measured on a binary scale.

In relation to the economic analysis i) costs associated with delivering the task sharing intervention, as well as the consequential impact on service use, will be analyzed using multiple regression analysis; bootstrap methods will be used if the residuals of the regression model are non-normally distributed. ii) Further regression models will include the main clinical measures so that the relationship between costs and outcomes can be assessed.

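### The sample size of 420 does not follow from its own stated inputs, which give about 306 to 342 women, and the 20% effect is not tied to the planned linear regression of HDRS-17

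*Protocol article*

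**What the plan says.** All of the inputs stand in the protocol article under Sample size and power calculation:

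- Error rates: "two-sided testing at alpha = 0.05, beta = 0.1 (i.e., 90% power".
- Control arm: "a 30 to 50% reduction in depressive symptoms at 3 months postnatally as measured by the HDRS-17 in the control arm".
- Effect: "Absolute effect sizes of interest range from 20 to 40" per cent.
- Attrition: "we feel that 10% attrition over the study period is realistic".
- Contamination: "5% of women in the control arm will experience the treatment effect of the intervention".

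The section presents these as the basis for its conclusion: "we estimate that 420 women in the trial will be required to detect an intervention effect of 20% or greater between the two arms", with 210 women in each arm.

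The analysis is given under Statistical methods: "The primary outcome measure will be analyzed using linear regression adjusting for baseline symptom severity measured using the HDRS-17". Under Objectives, the primary hypothesis refers to a 40% reduction on the HDRS. It does not say whether 40% is a threshold that each woman must reach or a difference between the arms.

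**The concern.** There are two problems in the one paragraph.

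First, the section lists its assumptions and offers 420 as their result, so a reader should be able to recompute it. The inputs are all percentages with no SD, which is the form of a two-proportion calculation, and that calculation gives a clearly smaller number.

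Second, the primary analysis compares mean HDRS-17 scores. A percent-scale effect without an SD or a difference in scale points cannot be converted into power for that comparison. The wording leaves open whether the percentages are proportions of women who respond or mean percent changes.

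The stated power and detectable effect are what readers will hold a null or small result against. As written, the figures do not match their own inputs, and they are on no defined scale for the analysis that will be run.

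**Working it through.** **Inputs from the document.** Two-sided alpha 0.05 (z = 1.960); power 0.90 (z = 1.282); control proportion pc = 0.30, 0.40 or 0.50; absolute effect 0.20; attrition 0.10; contamination 0.05; 210 per arm.

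**1. Trying to reproduce 420 as a two-proportion comparison.** If 5% of control women receive the effect, the control proportion becomes p1 = pc + 0.05 × 0.20 = pc + 0.01. The treated proportion is p2 = pc + 0.20, so the contrast is 0.19. With p̄ the mean of p1 and p2, the number per arm is

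n = [1.960 √(2p̄(1−p̄)) + 1.282 √(p1(1−p1) + p2(1−p2))]² / 0.19²,

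which is then divided by 0.90 for attrition. For 31% against 50%, p̄ = 0.405 and n = (1.361 + 0.873)² / 0.0361 = 138.2. Dividing by 0.90 gives 153.5, so 154 per arm.

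| p1 vs p2 | n per arm | after attrition | total | total with continuity correction |
|---|---|---|---|---|
| 0.31 vs 0.50 | 138.2 | 153.5 | 308 | 332 |
| 0.41 vs 0.60 | 143.4 | 159.4 | 320 | 342 |
| 0.51 vs 0.70 | 137.0 | 152.3 | 306 | 328 |

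Rounding up before dividing by 0.90 moves a total by at most 2. So 420 is 31 to 37% above the uncorrected totals (420/320 = 1.31; 420/306 = 1.37) and 23 to 28% above the corrected ones (420/342 = 1.23; 420/328 = 1.28).

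**2. Other routes to 420.**
- Contamination in both arms together with a continuity correction reaches at most 380.
- Treating contamination as a loss of 5 whole points (contrast 15 points) overshoots, at 484 to 514, and is not how the section defines contamination.
- Raising power to 97% gives 428 to 448, but the stated power is 90%.
- With everything else as stated, 420 is needed only if attrition is about 32 to 35% (1 − 143.4/210 = 0.32; 1 − 137.0/210 = 0.35), or about 27 to 30% with a continuity correction. The stated figure is 10%.

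**3. What 420 delivers on this reading.** Evaluable women per arm: 210 × 0.90 = 189. Power for a 20-point effect (19 after contamination) is 96.7%, 96.1% and 96.8% for pc of 0.30, 0.40 and 0.50. The uncontaminated difference detectable with 90% power is 17.0 to 17.5 points.

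**4. The planned regression.** Without baseline adjustment, the standardised difference detectable with 90% power is (1.960 + 1.282) × √(2/189) = 0.333 SD. Contamination shrinks the contrast to 95% of its size, so the uncontaminated difference is 0.333/0.95 = 0.351 SD. If the correlation between baseline and follow-up is assumed to be 0.5, the factor √(1 − 0.25) = 0.866 gives 0.289 SD, and 0.289/0.95 = 0.304 SD. The document gives no such correlation.

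**5. If the percentages are mean percent changes.** A 20-point difference is 19 points after contamination, and 90% power needs an SD of at most 19/0.333 ≈ 57 points (unadjusted). Since no SD is stated, a range is shown:

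| assumed SD of percent change | power at 189 per arm |
|---|---|
| 50 points | 96% |
| 57 points | 90% |
| 60 points | 87% |
| 70 points | 75% |

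**The case against.** The strongest reply is that the error lies in the safe direction. The section claims 90% power for an effect of 20% or more, and on the only reading that can be computed, 420 women meet that claim with margin. The word shown to be wrong is the one that calls 420 required. This stands, and it sets the weight of the point.

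A second reply is that a journal article condenses a fuller protocol and an analysis plan, and the SD or a further allowance may be given there. This stands in part: the absence of an SD is not by itself a fault. But the section offers its own list of assumptions as the basis for 420, and that list gives another number. The change of scale between the sample size and the analysis is also visible within the article.

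Three stronger readings are tempting and are not supported.

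- A reader might infer that the trial is underpowered. On the two-proportion reading the opposite holds. On the continuous scale power is undetermined: nothing in the document suggests an SD above 57 points, and baseline adjustment would be expected to help.
- A reader might take the 20% as relative to the control figure, which would need far more women. The section calls its effect sizes absolute.
- A reader might want power reduced for clustering of women by counsellor. The document gives no intraclass correlation, so any such figure would rest on an outside assumption, and it is a separate question from whether 420 follows from the stated inputs.

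**Conclusion.** The point holds in a limited form. The stated inputs give 306 to 320 women, or 328 to 342 with a continuity correction, so 420 is not what they require. This rests on reading the percentages as proportions of women, with contamination in the control arm only and attrition applied by division. No standard variant with the stated alpha, power and attrition reached 420 (see step 2).

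On that reading the trial has about 96 to 97% power for 20 points where the section says 90%, and 90% power for about 17 to 17.5 points. For the baseline-adjusted regression, the 90% claim is unverified from this text. It has not been shown to be false. The paragraph should be corrected because it governs how the result is read, but the conduct of the trial is not in doubt.

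**What to change.** Keep 420 and rewrite the sample size paragraph.

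1. Say whether the 20% is a difference in the proportion of women who respond (and at what threshold) or a difference in mean percent change.
2. Give the detectable difference for the planned regression. With 378 evaluable women, power is 90% for about 0.35 SD after contamination, unadjusted, or about 0.30 SD if a baseline correlation of 0.5 is assumed. State the assumed HDRS-17 SD, so that this can be read in scale points.
3. If a responder comparison was the basis, state about 96% power for 20 points and 90% power for about 17 points, or name the further allowance that raises the total to 420.

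The cost is one reworded paragraph. Enrolment, assessments and analysis are unchanged.

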### Objectives

The overall objective of the trial is to determine the acceptability, effectiveness, cost-effectiveness, and potential sustainability of task sharing mental health care for maternal depression compared to enhanced usual care in South Africa.

The specific objectives are:To determine the effectiveness and cost-effectiveness of a task sharing psychological intervention delivered by CHWs, compared to enhanced usual care in South Africa, on both primary outcome measures (of effectiveness and cost-effectiveness) and on a series of secondary outcome measures.To examine factors influencing the implementation of the task sharing intervention and potential for future scale up by assessing acceptability, feasibility, sustainability, quality, and safety.To adapt and evaluate locally relevant but generalizable measures, including both symptom severity measures and functioning measures, for evaluating the effectiveness and cost-effectiveness of task sharing care for maternal depression.

The primary hypothesis of the trial is that mothers with depression who receive the task-shared care will have improved clinical outcomes, as defined by a 40% reduction in depressive symptoms measured on the Hamilton Depression Rating Scale (HDRS) at 3 months postnatally, compared to mothers who receive enhanced usual care.

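### Five consecutive missed appointments for one assessment point count as leaving the whole study, so a woman unreachable antenatally may no longer be sought for the 3-month primary outcome

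*Protocol article*

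**What the plan says.** The protocol article gives two drop-out rules in the same paragraph of Sample size and power calculation. The first concerns treatment: "Drop out from care is defined as three consecutive missed appointments, for either the counselling sessions or telephone calls". The second concerns the study: once a woman has "missed five consecutive follow-up assessment appointments for a specific assessment point, they will be deemed to have dropped out of the study".

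The same paragraph contains the article's one undertaking to keep collecting data despite disruption, and it covers a single group: "We will endeavor to continue to collect data from people who move out of the area provided they give informed consent to continued participation", if they can be contacted.

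Under Number and duration of visits, both arms "receive follow-up assessments at 1 month antenatally and 3 and 12 months postnatally". The primary hypothesis, under Objectives, concerns improvement "as defined by a 40% reduction in depressive symptoms measured on the Hamilton Depression Rating Scale (HDRS) at 3 months postnatally". Statistical methods states: "The primary analysis will be by intention-to-treat, and secondary analyses will be on a per protocol population", and also: "The primary outcome measure will be analyzed using linear regression adjusting for baseline symptom severity measured using the HDRS-17".

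**The concern.** The rule is triggered at one assessment point but takes effect on study membership. The antenatal assessment is the first of three follow-ups and precedes the primary time point. Taken at face value, failure to complete it after five attempts ends a woman's participation before her primary outcome is due. Failure at 3 months would likewise end the search for her 12-month assessment. In neither case need she have withdrawn consent.

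The stake is missing HDRS-17 scores at 3 months that could have been collected. Women who cannot be reached in late pregnancy are unlikely to be a random subset of those randomised, so the loss may bias the comparison as well as thin the data. An analysis plan can say how missing values are handled, but it cannot recover a measurement that nobody attempted.

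**Working it through.** **1. What the rule does, read against the other passages.**
- Trigger: five consecutive missed appointments for one assessment point.
- Stated consequence: dropped out of the study. The paragraph has a separate term for leaving care, so the wider word appears to be a choice.
- Order of assessments: 1 month before delivery, then 3 months after, then 12 months after. The gap from the first to the primary time point is 1 + 3 = about 4 months.
- Exceptions: none for the antenatal point. The undertaking on continued data collection covers women who move away and does not mention women deemed to have dropped out.
- Analysis: a linear regression of the 3-month HDRS-17 on arm and baseline HDRS-17. A woman with no 3-month score contributes no outcome to it.

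The article does not say whether a woman so classified is approached again. The natural reading for a field team is that she is not.

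**2. How many women.** The article gives no rate of antenatal non-contact and no rate of later recovery. Both inputs below are assumptions.
- Unreachable antenatally, 5–10%: 0.05 × 420 = 21; 0.10 × 420 = 42.
- Of these, reachable at 3 months, 50–70%: 21 × 0.5 = 10.5; 42 × 0.7 = 29.4.
- Outcomes lost through the rule: about 10 to 29, that is 2.5% to 7.0% of 420.
- For scale, the article's attrition allowance is 0.10 × 420 = 42.

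**3. Whether power is at risk.** The article gives no standard deviation, so its figures are read here as proportions: control 0.30 to 0.50, difference 0.20, two-sided alpha 0.05, 90% power, 10% attrition and 5% contamination. With contamination, p0 = control rate + 0.05 × 0.20 and p1 = control rate + 0.20.

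Sample size first: n per arm = [1.96√(2p̄(1−p̄)) + 1.2816√(p0(1−p0) + p1(1−p1))]² / (p1−p0)². At a control rate of 0.40, p0 = 0.41 and p1 = 0.60, which gives 144 per arm. After 10% attrition, 144/0.9 = 160 per arm, or 320 in total. Across control rates the total is 308–320, or 330–344 with a continuity correction. The article's 420 is not reproduced; it is larger than this reading requires.

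Power with n per arm assessed: Φ{[(p1−p0)√n − 1.96√(2p̄(1−p̄))] / √(p0(1−p0) + p1(1−p1))}. Let x be the extra share lost through the rule among women who would otherwise be assessed, on top of the stated 10%, so n = 210 × 0.90 × (1−x).

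| x | n per arm | Power at control 0.30 / 0.40 / 0.50 |
|---|---|---|
| 0 | 189.0 | 0.967 / 0.961 / 0.968 |
| 5% | 179.5 | 0.959 / 0.953 / 0.960 |
| 10% | 170.1 | 0.950 / 0.942 / 0.951 |
| 20% | 151.2 | 0.924 / 0.915 / 0.926 |

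The illustrative loss of 10.5 to 29.4 out of 420 × 0.90 = 378 is x = 2.8% to 7.8%, so it lies between the first and third rows. Power stays above 90% throughout.

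**The case against.** The strongest reply is that the sentence only classifies. It stands in a sample-size section, beside statements on attrition and non-replacement, and may simply define who is counted as lost. It does not say that contact stops or that later data are refused. That is a fair limit on how firmly the point can be put: the end of follow-up is the natural reading, not an explicit instruction. The reply does not remove the point. The article separates leaving care from leaving the study, and its undertaking to continue data collection covers only women who move away. A field team could reasonably stop scheduling a woman deemed to have dropped out.

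Several stronger readings are tempting and are not supported.
- A reader might infer that missing the antenatal assessment is enough. It is not: the rule needs five consecutive missed appointments for that point, and a woman seen at an earlier attempt is unaffected.
- A reader might infer a contradiction with intention-to-treat. The rule neither removes a randomised woman from the analysis set nor changes her arm. It affects completeness of data, and the handling of missing outcomes may sit in the analysis plan, which the article says exists but which is not shown.
- A reader might infer that the rule causes different loss in the two arms, because one has six sessions and the other three calls. Those are care contacts. Assessments follow one schedule in both arms and are done by blinded field workers independent of the community health workers. Differential loss is possible, but the article gives no sign that this rule produces it.
- Some of the women one would worry about are partly covered: those who move, as above, and suicidal participants, whom Ethical considerations retains unless their health or behaviour makes participation impossible.

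The 10% attrition allowance may also already include women lost under this rule. In that case the illustrative loss falls within the allowance and does not add to it.

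**Conclusion.** The point holds in a limited form and should be fixed. As worded, the rule turns a failure at one assessment point into study drop-out without withdrawal of consent, and it does not protect the primary time point. The likely harm is avoidable, possibly non-random missing HDRS-17 data at 3 months, and missing data at 12 months. This weakens what an intention-to-treat analysis is meant to deliver without breaching it.

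The size cannot be established from the article. The figure of about 10 to 29 outcomes depends on two assumed rates and on the reading that later contact stops. Any bias is unquantified. Loss of power is not the problem: under the proportions reading, power is still about 0.92 to 0.93 with a further 20% lost.

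**What to change.** Replace the study drop-out sentence with wording to this effect: *After five consecutive missed appointments for an assessment point, that assessment is recorded as missed. The participant remains in the study and is contacted for every later assessment point unless she withdraws consent or dies.* Bring the field procedures into line, so that a missed antenatal assessment does not close the 3- and 12-month ones.

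The cost is one sentence in the protocol, the matching field instruction, and a few extra contact attempts at 3 and 12 months. Sample size, schedule and analysis model are unchanged. The Trial status section describes the trial as recruiting, so the change can still protect assessments not yet due.
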